#### Additional Analyses

Subgroup analysis will be performed regarding alcoholic/non-alcoholic etiology. Unplanned additional analysis will be identified in the final article as *post hoc* analysis.

#### Changes in the Protocol and Premature Termination of the Study

In case of slow recruitment rate (<72 patients in 3 years), the TSC may decide an interim analysis. The analysis will only be available to the members of the TSC, who will decide whether the study should continue or not. The DMC will perform regular safety analyses and may ask the TSC for premature termination of the study in case of a safety issue. This scenario is not expected given the wide experience with simvastatin in the last two and a half decades. The TSC may suggest changes to the protocol (for example, in case of very slow recruitment rate or safety issues); in such cases, researchers, drug agencies, and ethics committees will be informed.

### Other Considerations

[name] will have access to the final trial dataset, but the study arm treatment labels will be blinded until analysis is finished, as explained above. *Post hoc* collateral studies may be performed by the study collaborators with the final database after approval by the sponsor, the TSC, and the central Institutional Review Board.

The results of the study will be reported following the CONSORT Statement (19). The results of the trial will be communicated to patients and researchers, and there will be no publication restrictions. The manuscript draft will be written by [name] and reviewed by the study collaborators.

## Discussion

Some patients suffer from recurrent episodes of AP or acute flares of CP, with their physicians being unable to offer any effective preventive medications. Most of them have alcoholic or idiopathic etiology (26), as this first episode may trigger other risk factors to induce new episodes of AP (sentinel AP event model) (27). Recurrent pancreatitis is a condition associated with great discomfort and decreased quality of life (28). In almost all cases, it is associated with severe pain and requires hospital admission. Patients are afraid to travel, lose days of work and leisure, and often feel desperate about the random nature of pancreatitis flares.

SIMBA aims to investigate whether simvastatin is useful for preventing new episodes of pancreatitis in recurrent AP and CP, avoiding the natural progression of disease (AP) to CP, or the development of exocrine or endocrine pancreatic insufficiency in patients with established CP. We will use fecal elastase to detect EPI; this test is associated to a high false-positive rate (29); for that reason, we choose a 100 mcg/g threshold, which has been suggested to detect severe EPI (16). Based on the studies described in the *Introduction*, we are looking for a new indication for a well-established drug [it was released for medical use in late 80s (30)]. It is an inexpensive drug without active patent; currently, in Spain, treatment with simvastatin 40 mg costs 2.17 euros (2.58 USD) per month. This is a researcher-driven study (we report no conflict of interest) and is financed by public and private grants from the Spanish Government, the Spanish Association of Gastroenterology, and the Alicante's Institute for Health and Biomedical Research (ISABIAL); none of these institutions have commercial interest in the results of the present trial. The PI promoter, the collaborating researchers and TSC members participate in the study in an altruistic manner, without receiving economic compensation. All these considerations, together with the triple-blind design, make SIMBA a solid and clinically relevant study.

The main potential issue will be recruitment rate, as the study criteria are very restrictive; for this reason, we made an important effort for many centers throughout Spain to join. Currently (April 2020), 47 patients have been recruited so far. Another potential issue is adherence to treatment: patients with new episodes of pancreatitis during the follow-up period may abandon the study. For this reason, an estimated 20% loss of follow-up rate was considered in the sample size calculation.

In conclusion, the SIMBA study is a researcher-driven triple-blind randomized placebo-controlled, parallel-group, multicenter trial aiming to compare recurrence of new episodes of pancreatitis in patients with recurrent AP or acute flares of CP, consuming simvastatin vs. placebo.

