## Abstract

**Background:** One in every four patients with a first episode of non-gallstone-related acute pancreatitis (AP) develops recurrent disease. Recurrent episodes of AP or acute flares of chronic pancreatitis (CP) are associated with decreased quality of life and progression of the disease. Besides removing the etiology of pancreatitis (which sometimes is not possible), there are no effective measures to prevent recurrence. Meta-analyses of randomized controlled trials, as well as epidemiological and cohort studies, suggest that statins may be protective against the development of index AP.

**Methods:** The SIMBA study is a triple-blind randomized placebo-controlled, parallel-group multicenter trial. Patients with recurrent AP or with acute flares of CP (at least two episodes in the last 12 months) will be randomized to receive simvastatin 40 mg daily or placebo. During a 3-year study period, 144 patients (72 per arm of treatment) from 26 centers will be enrolled. The patients will receive the study treatment for 1 year. The primary aim is to compare the recurrence of AP or acute flares in CP. Secondary endpoints include the incidence of new-onset diabetes mellitus, new-onset exocrine pancreatic insufficiency (EPI), new-onset imaging signs of CP, frequency of all-cause hospital admissions, severity of AP, adherence to treatment, and frequency of adverse events.

**Discussion:** The SIMBA trial will ascertain whether simvastatin, a safe, widely used and inexpensive drug, can change the natural course of recurrent pancreatitis.

**Trial Registration**: ClinicalTrials.gov Identifier: NCT04021498

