## Introduction

Acute pancreatitis (AP) is the third most common cause of hospital admission due to gastrointestinal disease (1). Gallstones and excessive alcohol intake account for most cases of AP. Recurrent AP (RAP) refers to the development of at least two separate documented episodes of AP with a period of resolution in between (2). Approximately 20% of the patients will relapse after a first episode of AP (2, 3). The approximate incidence of recurrent AP is likely 8–10 per 100,000 per year, and its prevalence is 110–140 per 100,000 populations (2). The relatively low frequency of relapse in biliary AP (close to 10%) (3) is due to the high effectiveness of cholecystectomy (4), but a first episode of AP due to alcoholic or other etiologies is associated with relapse in one in every four patients (2, 3). Currently, besides removing etiological factors (which is frequently not possible), there are no specific medical treatment that changes the natural history of RAP. RAP is an intermediate stage in the pathogenesis of chronic pancreatitis (CP) as a subset of RAP patients' transition to CP (one in every three patients) over their natural history (2, 5). Forty-five percent of patients with CP experience intermittent flares of pain according to a prospective cohort study (6). Intermittent pain in CP is associated with missed days of work, frequent need for hospitalization, and a decreased quality of life (6).

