### Secondary Endpoints

New-onset diabetes at the end of follow-up, according to the American Diabetes Association criteria (15). Blood levels of glycosylated hemoglobin at the end of follow-up will also be compared to baseline.New-onset exocrine pancreatic insufficiency (EPI) defined by fecal elastase-1 <100 mcg/g (16). Fecal elastase-1 levels at the end of follow-up will also be compared to baseline.Imaging signs of CP at the end of follow-up, defined as calcifications and/or dilated pancreatic duct (≥4 mm) (17), mainly on a CT scan, but endoscopic ultrasound and/or MRI are allowed, particularly in younger patients to avoid excessive exposure to ionizing radiation.Frequency of all-cause hospital admissions.Severity of AP according to the revision of the Atlanta Classification (moderate-to-severe vs. mild) (14).Adherence to treatment (percentage of the planned treatment consumed by the patient).Frequency of adverse events.

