### Treatment Protocol

Patients receive simvastatin 40 mg or placebo, one capsule daily for 1 year. In case of recurrence of AP or acute flares of CP, the patients are advised to continue the treatment as planned. Adherence to treatment is monitored in each outpatient visit (comparison of the number of capsules remaining in the container with the number of capsules that should remain).

According to patient exclusion criteria, endoscopic retrograde cholangio-pancreatography, parathyroid, biliary, and/or pancreatic surgery are discouraged during the treatment period. In case of undergoing any of these procedures, the patient will be included in the intention-to-treat analysis, but the Trial Steering Committee will decide whether that patient should be included in the per-protocol analysis or not (the decision will be taken before blinded statistical analysis).

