#### Sample Size Calculation

Based on a pilot retrospective internal non-published analysis of patients from AUGH meeting the study inclusion and exclusion criteria, a recurrence rate of 50% in 1 year in patients with placebo is expected. We powered the study to detect a 50% decrease in recurrence during the study period. According to the arcsine method, with an alpha level of 0.05, a statistical power of 80%, an expected 1-year recurrence in the placebo arm of 50 and 25% in the simvastatin arm, and a 20% loss of follow-up, 144 patients are needed (72 per treatment arm).

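### Natural-course and progression aims outrun one on-treatment year sized for recurrence alone, and the planned elastase and HbA1c comparisons are not fixed as between-arm effects (minor)

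*Protocol article*

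**What the plan says.** The protocol article states two sizes of aim.

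- **Wide.** The Abstract closes by saying the trial will ascertain whether simvastatin "can change the natural course of recurrent pancreatitis". The Discussion adds, beside the prevention of new episodes, the aim of "avoiding the natural progression of disease (AP) to CP, or the development of exocrine or endocrine pancreatic insufficiency in patients with established CP".
- **Narrow.** The end of the Introduction, the Primary Endpoint section and the concluding paragraph all speak of recurrence only.

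The design is as follows.

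- **Treatment Protocol:** "Patients receive simvastatin 40 mg or placebo, one capsule daily for 1 year". Under Recruitment and Follow-Up the last visit is at 12 months, and no observation after treatment is described.
- **Sample Size Calculation:** based on "an expected 1-year recurrence in the placebo arm of 50 and 25% in the simvastatin arm", with 80% power and 20% loss, giving 72 per arm.
- **Introduction:** a subset of patients with recurrent AP "transition to CP (one in every three patients) over their natural history". This is the only progression rate in the article, and it has no time base.
- **Secondary Endpoints:** new-onset diabetes, new-onset exocrine pancreatic insufficiency (EPI; fecal elastase-1 below 100 mcg/g) and imaging signs of CP. HbA1c and fecal elastase-1 at the end of follow-up are also to be compared with baseline.
- **Analysis:** the other secondary endpoints get a chi-square test, a t-test or Mann–Whitney test, or a paired t-test or Wilcoxon test, depending on the type of variable.

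**The concern.** The wide aim concerns disease progression. The design measures what happens during a single year on drug. Two difficulties follow.

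First, with no observation off treatment, a changed disease course cannot be told apart from fewer attacks while the drug is being taken. The new-onset comparisons, which carry the progression aim, rest on a sample size chosen for a much more frequent event. Imprecise results could then be read as no effect on progression, and a positive primary result could be described as a changed natural course.

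Second, the measures best able to show early functional decline are worded as a comparison with baseline, and paired tests are among the methods offered. A paired test within each arm says whether that arm changed over the year. It does not estimate the difference between simvastatin and placebo, and a significant change in one arm with a non-significant change in the other is not evidence of a treatment effect.

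**Working it through.** **1. The plan's own sample size.** Inputs from Sample Size Calculation: 50% vs 25%, alpha 0.05 (taken as two-sided), power 80%, loss 20%, arcsine method.

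- h = 2·asin(√0.50) − 2·asin(√0.25) = 0.5236
- n per arm = 2·[(1.960 + 0.842)/h]² = 57.26
- 57.26/0.80 = 71.6, so 72 per arm and 144 in total.

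The stated figure reproduces. It leaves about 57 evaluable patients per arm (72 × 0.80 = 57.6).

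**2. Progression to CP.** The article gives one in three without a time base. Assume it accrues at constant hazard over T years, so that the one-year risk is 1 − (2/3)^(1/T). Power is for a halving of that risk, by exact binomial enumeration of the uncorrected two-sided 0.05 chi-square test. Expected placebo events are 57 × the one-year risk.

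| T (years, assumed) | One-year risk | Placebo events, 57 per arm | Power, 57 per arm | Power, 35 at risk per arm (assumed) |
|---|---|---|---|---|
| 20 | 2.0% | 1.1 | 1.6% | 0.4% |
| 10 | 4.0% | 2.3 | 6.6% | 2.6% |
| 5 | 7.8% | 4.4 | 13.0% | 9.4% |
| 3 | 12.6% | 7.2 | 21% | 16% |
| All within the trial year | 33.3% | 19.0 | 55% | 36% |

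The last row takes the protocol's figure at its most favourable and still falls short of 80%. The 57-per-arm column is itself generous, because patients who already have CP are eligible and cannot newly progress to it. The article does not give their expected share. The 35 only illustrates the effect of removing them.

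**3. EPI and diabetes.** The article gives no rates. At assumed control risks of 5%, 10% and 20% with all 57 per arm at risk, expected placebo events are 2.9, 5.7 and 11.4, and power for a halving is 9%, 17% and 32%.

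**4. Continuous measures.** With 57 per arm, an unadjusted two-group comparison has 80% power for a standardised difference of 2.802 × √(2/57) = 0.52. If the baseline value correlates at ρ with the month-12 value, baseline adjustment reduces the residual variance by the factor 1 − ρ², so the detectable difference is smaller. The article gives no value for ρ.

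**5. Wording of the imaging endpoint.** The Abstract lists new-onset imaging signs of CP. Secondary Endpoints lists imaging signs at the end of follow-up. Read literally, the second would count patients who had those signs at entry, and those are not progression events.

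**The case against.** The strongest reply is that these are secondary endpoints. No power is claimed for them, lack of formal power on secondary endpoints is usual, and the main aim, the primary endpoint and the conclusion all concern recurrence. This stands, and it is why the point is minor. It does not remove the wide aim, which the Discussion places beside recurrence without any exploratory caveat.

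Several stronger readings are tempting and should not be taken.

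- *Progression is tested only by yes/no endpoints.* The article already plans comparisons of HbA1c and fecal elastase-1. What is open is whether these are between-arm comparisons. The Analysis section allows a two-group test as well as a paired one and does not say which applies.
- *There will be only a handful of events per arm, so the tests are almost certain to be null.* For CP this follows only from an assumed multi-year spread. The trial requires at least two episodes in the past 12 months, so its patients may progress faster than recurrent AP patients in general. For EPI and diabetes no documented rate supports it, and 20% risk would give about 11 placebo events.
- *The Discussion restricts the insufficiency endpoints to established CP.* That is Discussion prose. The Secondary Endpoints section sets no such limit.
- *The plan will report a null as no effect.* Nothing says so, and odds ratios with 95% confidence intervals are planned where applicable, which would show the imprecision.

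The phrase natural course could also be read as recurrence itself. That reading is possible for the Abstract, but not for the Discussion sentence, which names progression and insufficiency.

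**Conclusion.** The point holds as one about over-stated aims and an under-specified comparison. One on-treatment year, sized for recurrence, cannot establish a changed natural course. For progression to CP, power to detect a halving is about 2% to 13% with 57 per arm if the one-in-three figure is spread over 5 to 20 years, and about 55% if all of it fell within the trial year. The spread is assumed, and so is treating every patient as at risk, which flatters the power. For EPI and diabetes the range is about 9% to 32%, at assumed control risks of 5% to 20%. Separately, the planned HbA1c and fecal elastase-1 comparisons are worded in a way that permits within-patient tests, which do not estimate a treatment effect. Severity is minor: the sample size reproduces, and the primary analysis is untouched.

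**What to change.** 1. In Secondary Endpoints and Analysis, make the main comparison for the insufficiency objectives the between-arm difference in month-12 fecal elastase-1 and in month-12 HbA1c, each adjusted for its baseline value (ANCOVA, on a transformed scale or ranks if skewed). Both are already measured at baseline and at the last visit.
2. Report new-onset EPI, new-onset diabetes and new imaging signs of CP as exploratory, each among patients free of that condition at baseline, with counts and confidence intervals. Use the new-onset wording for imaging in both places.
3. In the Abstract and Discussion, limit the claim to recurrence during one year of treatment, in line with the Introduction and the concluding paragraph.

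The cost is wording and analysis specification only, with no added visits, tests or patients. The downside is a less ambitious claim on progression.

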## Ethics Statement

This study involving human participants was performed in accordance with the declaration of Helsinki as well as the Good Clinical Practice international ethical and scientific quality standards. The study was reviewed and approved by (Comité Ético de Investigación Clínica con Medicamentos del Hospital General Universitario de Alicante, CEIM HGUA, reference number 2016/26). The study was originally approved on July 29th 2016. Secondary approval was obtained from all local Institutional Review Boards. The patients/participants provided their written informed consent to participate in this study.

## Abbreviations

AEG: Spanish Association of Gastroenterology
CECT: contrast-enhanced computed tomography
AEMPS: Agencia Española de Medicamentos y Productos Sanitarios (Spanish Drug Agency)
AP: Acute Pancreatitis
AUGH: Alicantes University General Hospital
CEIC HGUA: Comité Ético de Investigación Clínica del Hospital General Universitario de Alicante (AUGH Institutional Review Board)
CP: Chronic Pancreatitis
CRF: Case Report Form
DMC: Data Monitoring Committee
ISABIAL: Alicante's Institute for Health and Biomedical Research
MRI: magnetic resonance imaging
EPI: exocrine pancreatic insufficiency
PI: principal investigator
SIMBA: SIMvastatin in the prevention of recurrent acute pancreatitis, a triple Blind rAndomized controlled multicenter trial
TSC: Trial Steering Committee.
